No concomitant disease or malignancy interfering with the study procedure or efficacy outcome measures, particularly no severe or uncontrolled cardiovascular disease (congestive heart failure NYHA III or IV, unstable angina pectoris, myocardial infarction within ≤ 3 months, significant arrhythmias) and no psychiatric disorders precluding understanding of information of trial related topics and giving informed consent

*CCA*: cholangiocarcinoma, *ECOG*: Eastern Cooperative Oncology Group, *RFA*: radio frequency ablation, *NYHA*: New York Heart Association Functional Classification, *MDT*: multidisciplinary team

Randomization to study treatment should occur within three weeks after eligibility criteria have been met. Study subjects will be randomized by the electronic CRF to arm A (intervention group) or B (control group) in 1:1 ratio, stratified by trial site and tumor location (perihilar vs. ductal). The procedure itself (i.e., endoscopic stenting with or without RFA) and randomization are on the same day.

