**Fig. 1 Fig1:**
[figure not shown]
ACTICCA-2 trial design. *CCA*: cholangiocarcinoma, *MDT*: multidisciplinary team, *RFA*: radiofrequency ablation, *SEMS*: self-expanding metal stent, *OS*: overall survival, *QoL*: quality of life

As per study protocol, the selection of the RFA device is up to the discretion of the investigator, given approval in this context. The device provides bipolar energy to perform partial or complete ablation of tissue in the biliary tract. The RFA procedure will be performed only once at the beginning of the study. The extent of RFA for each individual patient will be decided by the investigator during the procedure. Of importance, trial site is one of the stratification criteria for randomization of patients to account for a possible procedure-related effects. Subsequent stent replacements will be carried out without additional RFA regardless of patient randomization to the intervention or control group.

All patients in the trial will receive endoscopic stenting and palliative chemotherapy as SOC as is indicated by local standards and as recommended in current guidelines [2]. Patients receiving liver-directed local therapy for hilar lesions, such as internal or external radiation therapy or chemosaturation will be censored at time of treatment if already enrolled in the trial. Radiation therapy to distant tumor sites (e.g. bone) is allowed. There are no restrictions on medications or other treatments, including full access to palliative care and symptom management (including pain control) throughout the trial.

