The secondary endpoints will include OS, QoL, clinical event rate at 6 months, total days of over-night-hospital-stays during the trial period as well as safety (terminology and grading according to NCI CTCAE v5). Median OS will be calculated as a secondary outcome to generate data for larger clinical trials targeting OS as a primary endpoint. Following the fixed study follow-up period of 6 months, patients or primary care providers will be contacted every 3 months by telephone call. QoL will be assessed with EORTC QLQ-C30 [suppl. material Fig. 1] and EORTC QLQ-BIL21 [suppl. material Fig. 2] questionnaires at each of the three on-site study visits. Clinical events as defined by the primary endpoint, i.e. stent dysfunction leading to premature stent replacement and/or disruption of chemotherapy, will be counted at 6 months follow-up and reported as a time-independent clinical event rate. In addition, cumulative over-night-hospital-stays within the fixed 6 months follow-up period will be counted. Moreover, assessing the safety of intraductal RFA is a major aim of the study and will be investigated as a secondary endpoint. RFA-related events will be examined, documented, and graded according to NCI CTCAE v5.

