### Quality assurance and safety

Patient data will be collected in electronic case report forms (CRF). Three independent experts will be appointed to serve as an Independent Data Monitoring Committee (IDMC) and give expert advice and supervision entirely independent of the applicants and the medical institutions involved. The IDMC will conduct thorough safety assessments throughout the study and will review all RFA-related events and decide on trial continuation after every 10th RFA procedure. A “harm rate” of ≥ 20% (≥ 6 RFA-related grade ≥ 4 events among the first 30 patients in the intervention group) will be suggested to the IDMC as critical.

The ERC will be responsible to blindly review and to verify countable events in both study arms to reduce possible biases caused by lack of blinding of the investigators to the RFA procedure. In addition, regular monitoring visits will be conducted by the AIO-Studien-gGmbH to ensure protocol adherence of the sites. A safety event (adverse event (AE) as per ICH-good clinical practice (GCP)) is defined as any untoward medical occurrence or experience in a subject or clinical investigation subject. Worsening of a pre-existing medical condition (e.g. diabetes, migraine headaches, gout) will be considered a safety event if there is either an increase in severity, frequency, or an association with significantly worse outcomes. A possible safety event will be graded according to CTCAE v5 and will be reviewed by the investigator and is properly captured in the subjects’ medical records and the electronic CRF. CTCAE grade 1 and 2 will only be regarded a safety event, if judged as “clinically relevant” by the investigator or if interfering with treatment administration. CTCAE grade 3 and 4 will always be regarded as safety events.

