### Sample size calculation and statistical analysis

The sample size of 120, i.e., 60 patients per group, was calculated based on the two-sided log-rank test for time to first event analysis. Thereby, a power of 80% can be reached under the following assumptions and with a two-sided significance level of 5%. Based on previous reports [7, 9, 14, 20], the event rate at 6 months in the control group was estimated to be 50% and 25% in the intervention group resulting in a hazard ratio (HR) of 0.415. The follow-up will be fixed at 6 months. Furthermore, it was assumed that there will be a low loss to follow-up of 2.5% over six months and all patients stay within their treatment group within the observational period. PASS version 16.0.3 was used for the calculation of the sample size.

Descriptive analysis for baseline characteristics will be performed giving mean, standard deviation, median, and inter-quantile range for continuous data as well as counts and percentages for categorical data. Tests of statistical significance will not be undertaken for baseline characteristics; rather the clinical importance of any imbalance will be noted [22]. A modified ITT (mITT) population will be used for the primary endpoint analysis. The mITT population consists of all patients who will be randomized in the ACTICCA-2 trial and who will undergo endoscopic stenting.

Primary endpoint analysis will be conducted using a cause-specific Cox proportional hazards model comparing the two treatment groups regarding time to first event within 6 months with trial site as random effect (frailty) and tumor location (perihilar vs. ductal) and stent material (plastic vs. metallic) as fixed effects. An adjusted HR for the treatment effect with corresponding 95% CI and p-value will be given as well as cumulative incidences with 95% CIs. The secondary endpoint OS will be analyzed with the Cox proportional hazards model with a frailty for trial site and adjusting for stratification variable tumor location and the variable stent material. Mixed models will be used for further secondary endpoints (linear, logistic, or negative binomial as appropriate).

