The mITT population will also be used for the secondary endpoint analysis. As a sensitivity analysis for the primary event of interest, results of the model by Fine and Gray will be given to take the competing event “death” into account. Cause-specific time-to-event analysis will be conducted for the components of the primary endpoint. Explorative subgroup analyses will be conducted in the same manner as for the primary outcome. Further sensitivity analysis will be conducted for the primary outcome, i.e., analysis for the per protocol population. The per protocol population includes all patients without major protocol violations. Furthermore, safety analyses will be conducted by the ERC/IDMC throughout the trial to decide about trial continuation after every 10th RFA procedure. Interim analyses are not planned. Missing values will not be imputed. Only the primary endpoint is analyzed in confirmatory manner with a two-sided significance level of 5% and all other analysis are considered explorative. Hence, no adjustment for multiple testing is conducted. A detailed statistical analyses plan will be prepared and finalized before the randomization code is broken. Data will be analyzed according to the Consolidated Standards of Reporting Trials (CONSORT) statement [23]. Statistical analyses will be carried out with an established statistical software such as SAS (Cary: SAS Institute Inc.; 2013.), Stata (College Station: StataCorp LLC.; 2021), R (Vienna: R Foundation for Statistical Computing; 2023.), or SPSS (Armonk: IBM Corp; 2021.).

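### Safety is placed in the mITT set with no analysis by RFA actually received; if some of arm A were stented without RFA, the by-arm comparison of harms could be diluted (minor)

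*Protocol article*

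**What the plan says.** Under Endpoint definition, safety is one of the secondary endpoints, and the article adds that "assessing the safety of intraductal RFA is a major aim of the study and will be investigated as a secondary endpoint". The same section says "RFA-related events will be examined, documented, and graded according to NCI CTCAE v5".

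Under Sample size calculation and statistical analysis, the population is fixed: "The mITT population consists of all patients who will be randomized in the ACTICCA-2 trial and who will undergo endoscopic stenting". The same set is then carried over: "The mITT population will also be used for the secondary endpoint analysis". The only other set named is per protocol, and it serves a sensitivity analysis of the primary outcome. No set or grouping by treatment received appears. The section makes all non-primary analyses explorative and announces a detailed SAP, which is not at hand.

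On delivery of RFA, the arm A section says that it is applied once, and the sample size assumptions have no patient leaving the allocated group. Treatment and trial procedures says: "The extent of RFA for each individual patient will be decided by the investigator during the procedure". Patient selection and randomization says: "The procedure itself (i.e., endoscopic stenting with or without RFA) and randomization are on the same day".

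Under Quality assurance and safety, the IDMC is to "decide on trial continuation after every 10th RFA procedure", while the suggested critical harm rate is "≥ 6 RFA-related grade ≥ 4 events among the first 30 patients in the intervention group".

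**The concern.** An efficacy-type set suits efficacy, where keeping patients as allocated protects the randomized comparison and non-receipt usually makes the result conservative. For harm, the same property works the other way. A patient allocated to RFA but stented without it adds to the arm A denominator without exposure, and a control ablated in error would count as unexposed. Either would tend to pull a between-arm comparison of adverse events towards no difference.

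The Study rationale says that early reports of hemobilia, cholangitis and stent obstruction make the value of RFA hard to judge, so this comparison matters. The article does not simply leave the safety population open. It assigns one, and a SAP that follows the sentence as written would have no table by exposure.

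**Working it through.** **The plan's own safety figure.** 6 / 30 = 0.20, so the stated 20% reproduces. Its denominator is patients in the intervention group, whereas the IDMC reviews are timed by RFA procedures. If k of the first 30 had no RFA, six events among the ablated patients would be 6 / (30 - k):

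- k = 1: 20.7%
- k = 2: 21.4%
- k = 3: 22.2%
- k = 6: 25.0%

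**Dilution between arms.** Let p1 be the adverse event rate with RFA, p0 the rate without, and f the share of arm A stented without RFA. If non-recipients carry background risk:

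- arm A rate = (1 - f) × p1 + f × p0
- by-arm excess = (1 - f) × (p1 - p0)

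The article gives none of these three inputs. Assumed here: p0 = 10%, p1 = 20% and f from 0 to 20%. The 60 patients per arm are the article's.

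| f | Arm A patients without RFA | Arm A rate | By-arm excess |
|---|---|---|---|
| 0% | 0 | 20.0% | 10.0 points |
| 5% | 3 | 19.5% | 9.5 points |
| 10% | 6 | 19.0% | 9.0 points |
| 20% | 12 | 18.0% | 8.0 points |

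Grouped by RFA received, the excess is 10 points in every row under the same assumption.

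**RFA-related events.** These cannot arise without RFA, so only the denominator is affected: observed rate = (1 - f) × p1. A 20% rate would read 19% at f = 5% and 16% at f = 20%.

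**Precision.** With 60 per arm, the standard error of the difference is √(0.20 × 0.80/60 + 0.10 × 0.90/60) = 6.5 points, so the 95% interval is about ±12.7 points. The shift of 0.5 to 2 points is small beside it.

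**If non-recipients are at higher risk.** Assume that 6 of 60 arm A patients miss RFA and have a 40% risk, with 20% in the 54 ablated patients and 10% in controls.

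- By arm: (54 × 0.20 + 6 × 0.40)/60 = 22%, an excess of 12 points.
- As treated: the unexposed rate is (60 × 0.10 + 6 × 0.40)/66 = 12.7%, an excess of 7.3 points.
- Ablated patients against controls: 10 points.

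The by-arm figure overstates only if controls do not share the raised risk, for example because an abandoned attempt caused it. If the control arm holds the same share of such patients, its other 54 have a risk of (6 - 2.4)/54 = 6.7%. The excess in patients who can be ablated is then 13.3 points, and the by-arm figure is again 0.9 × 13.3 = 12. In both readings the as-treated figure is too low.

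**The case against.** A reader might infer that the plan states a safety analysis by randomized arm and will therefore understate the harm of RFA. The documents do not support that, for four reasons.

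- **Grouping is not stated.** The article fixes who is in the mITT set, not how its members are grouped for safety. Grouping by allocation is the ordinary meaning of the label, and the SAP may settle it otherwise.
- **No non-receipt is foreseen.** The arm A section and the sample size assumptions both take delivery for granted. The sentence on extent concerns how much tissue is ablated, not whether ablation may be omitted.
- **Part of the safety work already follows exposure.** RFA-related events are the events named for grading, and IDMC reviews are counted in RFA procedures.
- **The direction is not certain.** Grouping by treatment received has its own selection bias and can also make RFA look safer than it is.

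Two further points carry weight. Cholangitis is also part of the primary endpoint, where allocation is the right grouping, and safety is explorative with wide intervals.

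All of this stands as a limit on the point, but it does not remove it. The sentence assigning the mITT set makes no exception for safety, and that set does not require ablation. The selection bias is a reason to show both tables, not to show only one.

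**Conclusion.** The point holds in a limited form, as a minor one. The article places safety, a major aim, in an efficacy-type set whose members need not have received RFA, and it states no comparison by treatment received. Whether this biases anything depends on f, which the article does not give. The shift is nil if every arm A patient is ablated. It is 0.5 to 2 points on an assumed 10-point excess for f of 5% to 20%, provided that non-recipients carry background risk. It may go the other way if they carry a raised risk that controls do not share. The conclusion also rests on reading mITT in its usual sense, grouped by allocation. No stated figure is wrong, and the efficacy analysis is unaffected.

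**What to change.** Except safety from the sentence that assigns the mITT set to secondary endpoints, and carry the change into the SAP. Analyse safety in all patients whose index procedure was begun, grouped by whether any RFA energy was applied. RFA precedes stenting, so this also keeps a patient who was ablated but not stented, whom the mITT definition would drop. Show the table by randomized arm alongside, because the as-treated groups are not fully randomized, and report how many patients in each arm did and did not receive RFA. Leave efficacy endpoints grouped by allocation.

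The two counting bases under Quality assurance and safety, RFA procedures and patients in the intervention group, should be reconciled in the same edit, without any change to the threshold itself.

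The cost is a sentence or two of wording and one extra table. Receipt of RFA must be tracked anyway to trigger the IDMC reviews. Sample size, treatment and the primary analysis do not change.

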### Translational research

Within the current trial, tumor tissue, if available, bile fluid, plasma, and buffy coat will be collected to establish a biobank. Participation is optional. The aim of this translational research project is to assess the prognostic and predictive impact of different biomarkers in cholangiocarcinoma.

## Data Availability

Not applicable as this manuscript does not contain any original data. Data generated throughout this study will be published separately.

## Abbreviations

AE: Adverse event
BIL21: Module Questionnaire for cholangiocarcinoma and gallbladder cancer
CCA: Cholangiocarcinoma
CrP C-: reactive protein
CI: Confidence interval
CRF: Case Report Form
CONSORT: Consolidated Standards of Reporting Trials
CTCAE: Terminology Criteria for Adverse Events
ECOG: Eastern Cooperative Oncology Group
EORTC QLQ-C30: European Organization for Research and Treatment of Cancer Quality of Life Questionnaire-Core 30
ERC: Endpoint Review Committee
ERCP: Endoscopic Retrograde Cholangiopancreaticography
GCP: Good Clinical Practice
HR: Hazard ratio
ICF: Informed consent form
IDMC: Independent Data Monitoring Committee
IEC: Independent Ethics Committee
IIT: Investigator-initiated trial
ITT: Intention-to-treat
mITT: modified intention-to-treat
MDT: Multidisciplinary Team
NCI: National Cancer Institute
NNT: Number-needed-to-treat
NYHA: New York Heart Association
OS: Overall survival
PDT: Photodynamic therapy
QoL: Quality of life
RDE: Remote data entry
RFA: Radiofrequency ablation
SAE: Serious adverse event
SDV: Source Data Verification
SOC: Standard of care
PROBE: Prospective randomized open blinded evaluation
TNM: Classification of malignant tumors
